## 5.7 Study Drug

---

ABBV-467, manufactured by AbbVie, should be administered as an intravenous (IV) infusion via a central venous catheter (CVC) (e.g., peripherally inserted central catheter line, port line) once weekly (QW), for each 28-day cycle over at least a 30-minute period beginning on C1D1. For any particular dose level below 1.4 mg/kg, a peripheral IV may be used if/when CVC placement is unavailable or contraindicated (CVC use is mandatory for any dose 1.4 mg/kg or higher due to possibly increased risk of adverse local/skin reactions). Subjects receiving study drug via peripheral IV should be monitored closely for extravasation and/or local irritation (which, if observed, should be reported to Sponsor). Doses will be determined by dose-escalation decision rules; the starting dose is 0.16 mg/kg. ABBV-467 can be administered with or without food. The first dose of ABBV-467 on C1D1 will be administered at half the targeted dose for a given subject; subsequent doses will be administered at the full target dose. After completion of Cycle 1, ABBV-467 doses may be delayed for up to 1 day due to scheduling conflicts; delays longer than 1 day should result in the dose being skipped. If there is a less than 10% weight change from weight on C1D1, no dose adjustment is necessary.

During preparation of the dose for infusion and during infusion, the solution must be protected from light. As the phototoxic potential of ABBV-467 is unknown, subjects will be advised to limit sunlight exposure during participation in the trial.

Study drug will be administered at the site with appropriate medical support available to manage infusion reactions if they occur. The study site personnel will document compliance.

AbbVie will provide instructions for drug preparation. AbbVie will not supply drugs other than ABBV-467.

Study drug information is presented in [Table 3](#).

**Table 3. Study Drug Information**

| Investigational Product | Manufacturer | Mode of Administration | Dosage Form                           | Strength |
|-------------------------|--------------|------------------------|---------------------------------------|----------|
| ABBV-467                | AbbVie       | Intravenous            | Concentrate for Solution for Infusion |          |

Study drug will only be used for the conduct of this study.

Additional information on the investigational product is provided in the Operations Manual, Section 6.

## 5.8 Randomization/Drug Assignment

This is an open-label study; there is no randomization. As they are enrolled in the study, subjects will be assigned unique identification numbers. At the time of screening, assignment of unique subject numbers and dose assignments will be done via interactive response technology. For subjects who rescreen, the screening number assigned at the initial screening visit should be used.

## 5.9 Protocol Deviations

The investigator is responsible for complying with all protocol requirements, written instructions, and applicable laws regarding protocol deviations. Protocol deviations are prohibited except when necessary to eliminate an immediate hazard to study subjects. If a protocol deviation occurs (or is identified), the investigator is responsible for notifying IEC/IRB, regulatory authorities (as applicable), and AbbVie.

# 6 SAFETY CONSIDERATIONS

## 6.1 Complaints and Adverse Events

### Complaints

A complaint is any written, electronic, or oral communication that alleges deficiencies related to the physical characteristics, identity, quality, purity, potency, durability, reliability, safety, effectiveness, or performance of a product/device. Complaints associated with any component of this investigational product must be reported to AbbVie.

## Product Complaint

A product complaint is any complaint related to the biologic or drug component of the product or to the medical device component(s).

For a product this may include, but is not limited to, damaged/broken product or packaging, product appearance whose color/markings do not match the labeling, labeling discrepancies/inadequacies in the labeling/instructions (e.g., printing illegible), missing components/product, device not working properly, or packaging issues.

Product complaints concerning the investigational product and/or device must be reported to AbbVie within 24 hours of the study site's knowledge of the event. Product complaints occurring during the study will be followed up to a satisfactory conclusion.

## Medical Complaints/Adverse Events and Serious Adverse Events

An AE is defined as any untoward medical occurrence in a subject or clinical investigation subject administered a pharmaceutical product and which does not necessarily have a causal relationship with this treatment. An AE can therefore be any unfavorable and unintended sign (including an abnormal laboratory finding), symptom, or disease temporally associated with the use of a medicinal (investigational) product, whether or not the event is considered causally related to the use of the product.

Such an event can result from use of the drug as stipulated in the protocol or labeling, as well as from "special situations," such as accidental or intentional overdose, medication error, occupational or accidental exposure, off-label use, drug abuse, drug misuse, all which must be reported whether associated with an AE or not. Any worsening of a pre-existing condition or illness is considered an AE. Worsening in severity of a reported AE should be reported as a new AE. Laboratory abnormalities and changes in vital signs are considered to be adverse events only if they result in discontinuation from the study, necessitate therapeutic medical intervention, meets protocol-specific criteria (see Section 6.2 regarding toxicity management), and/or if the investigator considers them to be AEs.

The investigators will monitor each subject for clinical and laboratory evidence of AEs on a routine basis throughout the study. All AEs will be followed to a satisfactory conclusion.

An elective surgery/procedure scheduled to occur during a study will not be considered an AE if the surgery/procedure is being performed for a pre-existing condition and the surgery/procedure has been pre planned prior to study entry. However, if the pre-existing condition deteriorates unexpectedly during the study (e.g., surgery performed earlier than planned), then the deterioration of the condition for which the elective surgery/procedure is being done will be considered an AE.

If any of the following AEs are reported, then the following supplemental report must be completed.

| Adverse Event                                                                                                                                                                                                          | Supplemental eCRF              |
|------------------------------------------------------------------------------------------------------------------------------------------------------------------------------------------------------------------------|--------------------------------|
| All AEs that meet DLT criteria, per protocol Section 6.3, Dose-Limiting Toxicity                                                                                                                                       | Dose-Limiting Toxicity eCRF    |
| Discontinuation or interruption of study drug due to a hepatic-related AE
A hepatic-related SAE
Clinically significant hepatic AEs
ALT or AST $\geq 3 \times$ ULN along with total bilirubin $> 2 \times$ ULN | Hepatic AE eCRF                |
| All AEs of infusion related reaction regardless of causality                                                                                                                                                           | Infusion Related Reaction eCRF |
| AEs of overdose, abuse, off-label use, misuse, medication error, occupational exposure                                                                                                                                 | Special Safety Situations eCRF |
| Per protocol Section 6.2, Toxicity Management                                                                                                                                                                          | Tumor Lysis Syndrome eCRF      |

AE = adverse event; eCRF = electronic case report form; SAE = serious adverse event; ULN = upper limit of normal

If an AE, whether associated with study drug or not, meets any of the following criteria, it is to be reported to AbbVie clinical pharmacovigilance as a SAE within 24 hours of the site being made aware of the SAE (refer to Section 4.3 of the Operations Manual for reporting details and contact information):

|                                                           |                                                                                                                                                                                                                                                                                                                              |
|-----------------------------------------------------------|------------------------------------------------------------------------------------------------------------------------------------------------------------------------------------------------------------------------------------------------------------------------------------------------------------------------------|
| Death of Subject                                   | An event that results in the death of a subject.                                                                                                                                                                                                                                                                             |
| Life-Threatening                                   | An event that, in the opinion of the investigator, would have resulted in immediate fatality if medical intervention had not been taken. This does not include an event that would have been fatal if it had occurred in a more severe form.                                                                                 |
| Hospitalization or Prolongation of Hospitalization | An event that results in an admission to the hospital for any length of time or prolongs the subject's hospital stay. This does not include an emergency room visit or admission to an outpatient facility.                                                                                                                  |
| Congenital Anomaly                                 | An anomaly detected at or after birth, or any anomaly that results in fetal loss.                                                                                                                                                                                                                                            |
| Persistent or Significant Disability/Incapacity    | An event that results in a condition that substantially interferes with the activities of daily living of a study subject. Disability is not intended to include experiences of relatively minor medical significance such as headache, nausea, vomiting, diarrhea, influenza, and accidental trauma (e.g., sprained ankle). |

**Important Medical Event  
Requiring Medical or Surgical  
Intervention to Prevent  
Serious Outcome**

An important medical event that may not be immediately life-threatening or result in death or hospitalization, but based on medical judgment may jeopardize the subject and may require medical or surgical intervention to prevent any of the outcomes listed above (i.e., death of subject, life threatening, hospitalization, prolongation of hospitalization, congenital anomaly, or persistent or significant disability/incapacity). Additionally, any elective or spontaneous abortion or stillbirth is considered an important medical event. Examples of such events include allergic bronchospasm requiring intensive treatment in an emergency room or at home, blood dyscrasias or convulsions that do not result in inpatient hospitalization, or the development of drug dependency or drug abuse.

All AEs reported from the time of study drug administration until 30 days after discontinuation of study drug administration will be collected, whether solicited or spontaneously reported by the subject. In addition, study procedure-related serious and nonserious AEs will be collected from the time the subject signs the study-specific informed consent.

The following definitions will be used for Serious Adverse Reactions (SAR) and Suspected Unexpected Serious Adverse Reaction (SUSAR):

**SAR** Defined as all noxious and unintended responses to an IMP related to any dose administered that result in death, are life-threatening, require inpatient hospitalization or prolongation of existing hospitalization, result in persistent or significant disability or incapacity, or are a congenital anomaly or birth defect.

**SUSAR** A suspected SAR: refers to individual SAE case reports from clinical trials where a causal relationship between the SAE and the IMP was suspected by either the sponsor or the investigator, is not listed in the applicable Reference Safety Information, and meets one of the following serious criteria: results in death, is life-threatening, requires hospitalization or prolongation of an existing hospitalization, results in persistent or significant disability or incapacity, or is a congenital anomaly or birth defect. All individually reported SARs are considered suspected.

AbbVie will be responsible for Suspected Unexpected Serious Adverse Reactions (SUSAR) reporting for the Investigational Medicinal Product in accordance with global and local requirements.

Adverse events will be monitored throughout the study to identify any of special interest that may indicate a trend or risk to subjects.

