## APPENDIX D. ACTIVITY SCHEDULE

The following table shows the required activities for this study. The individual activities are described in detail in the Operations Manual Section 3.

Study Activities Table

| Activity                               | Screening
(Day -21 to Day -1) | Cycle 1, Day 1 | Cycle 1, Days 2 - 5 | Cycle 1, Days 8, 15,
22 (± 1 day) | Cycle 1, Days 16 &
17 | Day 1 of Each Cycle
(± 1 day) | Days 8, 15, 22 of
Each Cycle (± 1 day) | Final Visit | 30-day F-U Visit
(± 7 days) | Post-Treatment
Follow-Up (every
3 months ± 7 days) |
|----------------------------------------|----------------------------------|----------------|---------------------|--------------------------------------|--------------------------|----------------------------------|-------------------------------------------|-------------|--------------------------------|----------------------------------------------------------|
| INTERVIEWS & QUESTIONNAIRES |                                  |                |                     |                                      |                          |                                  |                                           |             |                                |                                                          |
| Informed consent                       | ✓                                |                |                     |                                      |                          |                                  |                                           |             |                                |                                                          |
| Eligibility criteria                   | ✓                                | ✓              |                     |                                      |                          |                                  |                                           |             |                                |                                                          |
| Medical/oncology history               | ✓                                | ✓              |                     |                                      |                          |                                  |                                           |             |                                |                                                          |

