| [figure not shown] LOCAL LABS AND EXAMS | 
 
Single 12-lead ECG
 
Vital signs
 
ECOG performance status
 
Targeted physical examination
 
                                                                                                                                                             | 
 
Weight
 
Urine pregnancy test
 
Coagulation/urinalysis
 
                                                                                                     |
| [figure not shown] CENTRAL LABS         | 
 
Hematology/chemistry
 
Peripheral blood biomarker samples
 
                                                                                                                                                                                                            | 
 
BM aspirate and biopsy biomarker samples
 
Optional biomarker samples (if consent given)
 
                                                                          |
| [figure not shown] DISEASE ASSESSMENT   | 
 
AML: BM aspirate and biopsy for response assessments
 
AML: response assessment
 
MM: Serum protein immunofixation, serum protein electrophoresis, serum quantitative immunoglobulins, serum FLC, urine protein immunofixation, urine protein electrophoresis
 
 | 
 
MM: skeletal survey/assessment of lytic disease, plasmacytoma evaluation (as clinically indicated)
 
MM: BM aspirate for response assessment, response assessment
 
 |

AML = acute myeloid leukemia; BM = bone marrow; ECG = electrocardiogram; ECOG = Eastern Cooperative Oncology Group; FLC = free light chain; MM = multiple myeloma

NOTES: -Final Visit procedures should be performed when a subject discontinues from the study.  
 -Final visit ECG may be obtained within  $\pm$  2 days of visit.  
 -See Section 3.16 for further details regarding required disease assessments.  
 -For AML and MM: BM biopsy and aspirate biomarker samples to be split from samples taken for disease assessments. See Section 3.8 for further details on biomarker sample requirements.

Follow-Up Visit (30 days post last dose,  $\pm$  7 days): [figure not shown]

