|                                                                                                        |                                                                                             |                                                                                              |
|--------------------------------------------------------------------------------------------------------|---------------------------------------------------------------------------------------------|----------------------------------------------------------------------------------------------|
| [figure not shown] INTERVIEW            | 

Adverse event assessment

                    | 

Prior/concomitant medications

                |
| [figure not shown] LOCAL LABS AND EXAMS | 

Vital signs

ECOG performance status

 | 

Targeted physical examination

Weight

 |
| [figure not shown] CENTRAL LAB          | 

Hematology/chemistry

                        |                                                                                              |
| [figure not shown] DISEASE ASSESSMENT   | 

Disease status

Survival status

      | 

Subsequent anticancer therapy

                |

ECOG = Eastern Cooperative Oncology Group

Post Treatment Follow-Up (Every 3 months post Follow-Up Visit,  $\pm$  7 days): [figure not shown]

|                                                                                                      |                                                                                        |                                                                               |
|------------------------------------------------------------------------------------------------------|----------------------------------------------------------------------------------------|-------------------------------------------------------------------------------|
| [figure not shown] DISEASE ASSESSMENT | 

Disease Status

Survival status

 | 

Subsequent anticancer therapy

 |

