## 4 SAFETY MANUAL

### 4.1 Methods and Timing of Safety Assessment

---

All serious and nonserious AEs which could be related to study procedures (e.g., occurrence during screening) will be collected from the time the subject signed the study-specific informed consent until study drug administration and reported to the sponsor. From the time of study drug administration until 30 days after discontinuation of study treatment, all AES and SAEs will be collected whether solicited or spontaneously reported by the subject.

[figure not shown]

AE = adverse event; SAE = serious adverse event

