## 4.2 Recording Data and Analyses of Safety Findings

Adverse events will be coded using MedDRA. The number and percentage of subjects with treatment-emergent adverse events (i.e., any event that begins or worsens in severity after initiation of study drug through 30 days post-study drug dosing) will be tabulated by primary MedDRA SOC and preferred term and compared between arms using Fisher's exact test. The tabulation of the number of subjects with treatment-emergent AEs by severity grade and relationship to study drug also will be provided. Subjects reporting more than 1 AE for a given MedDRA preferred term will be counted only once for that term using the most severe grade according to the severity grade table and the most related according to the relationship to study drug tables. Subjects reporting more than 1 type of event within an SOC will be counted only once for that SOC.

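### The last scheduled adverse-event assessment may be held up to 7 days before the 30-day collection window closes, and no later scheduled contact asks about adverse events

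*Protocol*

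**What the plan says.** Days below are counted from the last dose unless stated otherwise.

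**Collection window.** Protocol 6.1 states: "All AEs reported from the time of study drug administration until 30 days after discontinuation of study drug administration will be collected". It covers solicited and spontaneous reports alike. Operations Manual 4.1 repeats the rule: "until 30 days after discontinuation of study treatment, all AES and SAEs will be collected whether solicited or spontaneously reported by the subject".

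**Analysis window.** Operations Manual 4.2 defines a treatment-emergent event as "any event that begins or worsens in severity after initiation of study drug through 30 days post-study drug dosing". Protocol 7.5 restricts the AE analyses to treatment-emergent events, so Day 30 is also the boundary of what is tabulated.

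**Last scheduled enquiry.** Appendix D has a column for the "30-day F-U Visit" with a tolerance of 7 days either way. Operations Manual 2.2 describes the same visit as "Follow-Up Visit (30 days post last dose", with the same tolerance, and lists "Adverse event assessment" and central hematology/chemistry among its activities.

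**What follows.** The post-treatment contacts every 3 months cover disease status, survival and subsequent anticancer therapy. Their cells for AE assessment and for hematology/chemistry in Appendix D are blank. Operations Manual 2.2 allows these contacts to be made by phone or from records or public sources.

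**Any other contact near Day 30.** Protocol 5.6 mentions a 30-day phone call, but only for subjects who withdraw consent, and only if they are willing. No text asks for a further AE enquiry when the Follow-Up Visit is held early.

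**The concern.** The window for collecting and counting events ends at Day 30, but the schedule lets the last planned question about events be asked a week earlier. A site that sees a subject on Day 23 has complied with the schedule and has no planned occasion to ask about the remaining days.

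Characterising safety is the first primary objective (Protocol 3), and AE monitoring heads the primary endpoints (Protocol 3.1). An early visit can only lose events; it cannot add them. The length of solicited follow-up then differs between subjects by visit day, while the tabulations treat everyone as observed to Day 30. The last scheduled safety bloods sit at the same visit, and a subject cannot volunteer a laboratory abnormality that causes no symptoms. An analysis plan cannot repair this, because no analysis recovers events that were never asked about or measured.

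**Working it through.** The plan gives no figure of its own for this gap, so there is none to reproduce. The check is day arithmetic on the stated windows.

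**Inputs**
- End of collection and treatment-emergent window: Day 30 (Protocol 6.1; Operations Manual 4.1 and 4.2).
- Follow-Up Visit: Day 30 with a tolerance of 7 days (Appendix D; Operations Manual 2.2).
- AE item at later scheduled contacts: none (Appendix D; Operations Manual 2.2).

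**Permitted visit days.** Earliest 30 − 7 = Day 23; latest 30 + 7 = Day 37.

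**Days without a scheduled enquiry.** For a visit on day d, the gap is max(0, 30 − d).
- d = 23: 30 − 23 = 7 days (Days 24 to 30), and 7/30 = 23.3% of the window.
- d = 30 to 37: gap 0.

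**A rough average.** The documents do not say when visits actually fall. If they were spread evenly over the 15 days from Day 23 to Day 37 (an assumption), the mean gap would be (7 + 6 + 5 + 4 + 3 + 2 + 1 + 8 × 0)/15 = 28/15 = 1.9 days, and 1.87/30 = 6.2% of the window. With every visit on the earliest day it is 23.3%; with none before Day 30 it is 0.

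**Dose-escalation decisions.** These count dose-limiting toxicities (DLTs) in the first 28-day cycle (Protocol 4.1 and 6.3). A subject who receives all Cycle 1 doses is last dosed in that cycle on study Day 22, so the earliest nominal Follow-Up Visit is study Day 22 + 23 = Day 45. That is after the 28-day period and after the study Day 42 time point for hematologic DLTs in AML. The other AML time point, 14 days after stopping, also comes before Day 23 after the last dose.

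**After the change.** With an enquiry on or after Day 30 for every subject seen early, the largest gap in AE enquiry falls from 7 days to 0.

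**The case against.** The strongest reply is that nothing is contradicted. The 7 days are a scheduling tolerance for one visit and do not shorten the duty to collect events to Day 30. Other provisions reach into Days 24 to 30:

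- Protocol 6.1 has investigators monitor for AEs routinely throughout the study and follow every AE to a satisfactory conclusion, so an event open on Day 23 prompts further contact.
- Serious AEs are reportable within 24 hours of the site learning of them, by whatever route (Protocol 6.1; Operations Manual 4.3).
- Medication that becomes necessary, and the reason for it, is recorded through 30 days after the last dose (Operations Manual 3.3).
- Deaths are picked up by survival follow-up.

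The trial has no control group and no randomisation, so uneven visit days do not bias a between-group comparison.

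Most of this stands, and it limits the point. A reader might infer that all events on Days 24 to 30 go uncollected, or that a quarter of post-treatment safety data is lost. The documents do not support that: the recording duty remains, and 23.3% is a share of days for a subject seen at the earliest edge, not a share of events or of subjects. A reader might also infer that delayed toxicity in particular is missed, but the documents report no toxicity with onset in that week.

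A third tempting step is that the gap exceeds 7 days, because Protocol 6.1 counts from discontinuation while the visit counts from the last dose. That would follow only if discontinuation were dated later than the last dose, for example after a dose hold. The documents do not say so, and Operations Manual 4.2 ties the analysis window to dosing.

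What the reply does not remove is that none of these provisions is a scheduled AE enquiry or laboratory test after an early visit.

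**Conclusion.** The point holds in a limited form. The schedule permits the last planned AE assessment, and the last planned safety bloods, on Day 23, while events are to be collected and counted through Day 30. The worst case is 7 of 30 days (23.3%) without a scheduled enquiry or test; it is nil for visits on Days 30 to 37 and averages about 6% under the even-spread assumption. The likely loss is mainly new non-serious events and symptomless laboratory abnormalities in subjects seen early. DLT-based dose decisions are untouched.

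This rests on reading the 30 days from the last dose and on taking the listed activities as the full set of scheduled contacts. It is worth correcting because safety is a primary objective, any loss can only be under-reporting, and the remedy is cheap.

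**What to change.** In Appendix D and Operations Manual 2.2, keep the ± 7-day window and add one line: if the Follow-Up Visit takes place before Day 30, the site makes an AE enquiry by phone on or after Day 30, covering events through Day 30. The cost is one short call for subjects seen early. A call does not replace a blood test, so a symptomless laboratory abnormality arising after an early visit could still be missed.

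The alternative is to set the window to Day 30 + 7 days only, which brings the bloods to Day 30 or later as well. Its cost is that more visits may fall after new anticancer therapy has started, which makes attribution harder; Protocol 5.6 says that its discontinuation procedures should not hold up new treatment. For that reason the phone enquiry is preferable.
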